### Interventional phase

The primary and secondary comparative analyses and presentation of this randomised trial will be in accordance with CONSORT guidelines and based on the intention-to-treat (ITT) principle without imputation of missing values (complete case population). The intention-to-treat population uses all randomised participants in the groups they were randomised to regardless of the intervention received and the complete case population restricts the population to include all randomised participants with complete data and follow-up. ITT analysis with missing values imputed will be undertaken as a sensitivity analysis.

### Primary analysis

For those who enter the interventional phase of the study, the primary outcome will compare the total number of units of allogeneic products (red blood cells, FFP, cryoprecipitate, and platelets) transfused after study medication until discharge from hospital between women who received fibrinogen concentrate and placebo. A Poisson regression model will be used with due emphasis placed on confidence intervals for the between-arm comparisons with an investigation of site-level clustering. The primary analyses will also be repeated controlling for any baseline imbalances. While the main analyses will be based on ITT without imputation, we will undertake sensitivity analyses in order to estimate the effect of those randomised to fibrinogen but not receiving it using complier average causal effect (CACE) estimates, implemented in Stata using instrumental variable regression [24].

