### Sample size

On the basis of data prospectively collected in Cardiff in a study with the same entry criteria as this trial, the sample size was derived in the following way:

From a group of women with on-going bleeding (further bleeding of ≥250 ml after enrolment) and with a Fibtem A5 < 16 mm (representing women who would be the control/placebo group), the total number of allogeneic units (red cells + FFP + cryoprecipitate + platelets) transfused was positively skewed. The data were therefore transformed using the natural log (x + 1) transformation. This resulted in a more normal distribution with a mean [standard deviation (SD)] of 1.811 (1.004) on the log-transformed scale. Back-transforming this data gives a geometric mean of 5.12 units of allogeneic blood transfusions. Using the data from low-risk women with Fibtem A5 > 22 mm (representing what we would expect in the intervention group) then using the same transformation, the mean (SD) is 0.256 (0.539). Back-transforming gives a geometric mean of 0.30 units of allogeneic blood transfusions. This demonstrates a difference of 1.811-0.256 = 1.556 on the log-transformed scale.

A total of 60 patients can realistically be recruited. Therefore basing our sample size calculation on 27 per group (54 in total plus a 10% dropout), if the mean on the transformed scale in the intervention group is 1.036, this is the size of difference that we would be able to detect with power 80% at the two-sided 5% alpha level [22]. A transformed mean of 1.036 corresponds to a back-transformed ‘geometric mean’ of 1.81 allogeneic units. This is a 3.3 unit reduction, when measured as a simple difference on the original scale. The size of difference between control and intervention groups we might assume from this, when expressed on the log-transformed scale, is 1.811-1.036 = 0.775.

In the light of the difference found between the high- and low-risk groups (1.552), the assumption we are making for the new study still appears to be cautiously conservative. Thus we conclude that 27 individuals in each treatment arm (54 in total) would give 80% power to attain a difference of 3.3 total allogeneic units (0.775 on a log-transformed scale) at a conventional 5% alpha level. Assuming a 10% loss to follow-up, this will enable 60 women (30 per treatment group) to complete the trial and achieve the above numbers.

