### Setting, location and follow-up

The study will recruit from four centres in the UK. The criteria for selection are based on size of the centres (a minimum of approximately 5500 deliveries per year) and an interest in peripartum clinical studies. The study team at each centre will be based on delivery suite and consist of a lead obstetrician, obstetric anaesthetist and midwife. All obstetricians, obstetric anaesthetists and midwifes at each centre will be involved in the study.

Women recruited to the observational phase, but who do not enter the interventional phase of the study, will be followed up until hospital discharge. Women participating in the interventional phase will be followed up until 6 weeks following randomisation or death. At 6 weeks post-delivery, women who entered the interventional phase of the study will be contacted by telephone. The telephone interview will obtain data on maternal hospital readmissions, incidence of venous or arterial thrombotic events, and initiation and duration of breastfeeding.

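### The primary analysis is called ITT, but its outcome clock, its completeness rule and one explicit exclusion, as written, leave out randomised women whose unit totals could be known

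*Protocol article*

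**What the plan says.** All references are to the protocol article.

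- **Population** (Statistical methods, Interventional phase): primary and secondary comparisons follow ITT, defined as every randomised woman in her assigned group whatever treatment she got. The main analysis is without imputation, and "the complete case population restricts the population to include all randomised participants with complete data and follow-up". ITT with imputation is a sensitivity analysis.
- **Outcome window** (Outcomes and safety measures; Primary analysis): units are counted from study medication to hospital discharge. The comparison is of units "transfused after study medication until discharge from hospital between women who received fibrinogen concentrate and placebo".
- **Non-receipt** (Primary analysis): the main analyses are again called ITT, and sensitivity analyses will "estimate the effect of those randomised to fibrinogen but not receiving it using complier average causal effect (CACE) estimates".
- **Follow-up** (Setting, location and follow-up): women in the interventional phase are followed for six weeks, when "women who entered the interventional phase of the study will be contacted by telephone". The call covers readmissions, thrombotic events and breastfeeding. None of these enters the primary outcome.
- **Early access to results** (Methods and design, Interventional phase): a woman whose 15-minute coagulation results are looked at before the FFP decision is left out of the primary efficacy analysis.

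**The concern.** The protocol fixes both the outcome and the analysis population, and the two do not fit together. Three rules act after randomisation: whether the infusion was given, whether follow-up was complete, and whether results were accessed early. Each can take a woman out of an analysis that is said to include everyone randomised.

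What is at stake is mainly comparability. Early access happens when the clinical situation calls for it, about 15 minutes after the infusion. It may therefore be related to bleeding severity and, if the drug works, to the allocated arm. Non-infusion may also be related to the course of the bleed, although the article does not say why or how often it would occur. With 30 women per arm, each woman lost is about 3% of her arm (1/30).

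**Working it through.** **Step 1. Set the rules side by side.**

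| Randomised woman | ITT definition | Other rule | Result as written |
|---|---|---|---|
| Never infused | Included | Count starts at study medication | No start time, so no defined outcome |
| Infused, total to discharge known, six-week call missed | Included | Complete data and follow-up required | Excluded if read literally; included if completeness is judged per outcome |
| Infused, 15-minute results accessed early | Included | Left out of the primary efficacy analysis | Excluded, with no other reading |
| Infused, complete, results not accessed early | Included | None | Included |

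The first row also affects the CACE. The instrumental-variable estimate is

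CACE = (mean outcome by allocation: fibrinogen − placebo) / (proportion receiving fibrinogen by allocation: fibrinogen − placebo).

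The numerator is the ITT difference, so it needs an outcome for every non-recipient. The quantity estimated is the effect among compliers; the article's gloss describes those who did not get the drug.

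**Step 2. Reproduce the design figure.** Inputs from Sample size: control "mean [standard deviation (SD)] of 1.811 (1.004) on the log-transformed scale"; the difference "is 1.811-1.036 = 0.775"; two-sided 5% alpha, 80% power; 1:1 allocation.

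- n per arm = 2 × (1.96 + 0.842)² × 1.004² / 0.775² = 2 × 7.85 × 1.008 / 0.6006 = 26.3, rounded up to 27. The t-test version gives 27.3.
- 54 / 0.90 = 60. The stated 27, 54 and 60 all reproduce.

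**Step 3. Power by number lost.** Power = Φ(0.775 / (1.004 × √(2/n)) − 1.96).

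- n = 27: 0.775 / 0.2733 = 2.836; Φ(0.876) = 81.0% (t-test 79.5%).
- n = 30: 0.775 / 0.2592 = 2.990; Φ(1.030) = 84.8% (t-test 83.6%).

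The article does not give the number that would be lost, so a range is assumed, split equally by arm (t-test power):

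| Lost of 60 | 0 | 3 | 6 | 9 | 12 | 18 |
|---|---|---|---|---|---|---|
| Power | 83.6% | 81.7% | 79.5% | 77.1% | 74.5% | 68.5% |

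**Step 4. Illustrate selective loss.** Assume no treatment effect and log-scale values that are normal with mean 1.811 and SD 1.004. By simulation, removing the heaviest-transfused women from one arm of 30 moves that arm's log mean as follows:

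- 1 woman: −0.07, or 0.071/0.775 = 9% of the design effect
- 2 women: −0.13, or 0.131/0.775 = 17%
- 3 women: −0.19, or 0.187/0.775 = 24%

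This is a worst case (only the heaviest, only one arm), not a forecast.

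**The case against.** Several points on the other side are sound.

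- **A reader might infer an as-treated primary analysis from the word *received*.** The article does not support that. It defines ITT explicitly, repeats in Primary analysis that the main analyses are ITT, and speaks in Outcomes and safety measures of comparing the two arms. One loose phrase should be reconciled with these statements.
- **A reader might infer that women with known totals will be lost for missing the call.** That is not established. The complete-case wording explains what no imputation means and covers primary and secondary outcomes together, so completeness per outcome is a natural reading. Participant flow and recruitment lists women completing the protocol separately from those analysed for the primary outcome. Imputed ITT would also bring women back, though only as a sensitivity analysis.
- **A reader might infer that uninfused women cannot enter any analysis.** Planning a CACE suggests that the authors expect outcome data on them, and a substitute start time could sit in the SAP. The protocol's own outcome definition still gives them none.
- **The power figures show no design failure.** The 10% allowance already brings 60 down to 54, so 83.6% is a surplus. Sample size speaks only of loss to follow-up, without saying at what time. The figures are for a t-test on ln(x + 1), whereas the planned model is Poisson regression.
- **Moving the clock for every woman alters a stated primary outcome** after 16 women had been randomised. The gap can be closed with less.

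None of this answers the early-access exclusion, which is explicit and conflicts directly with the ITT definition.

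**Conclusion.** The concern holds in a limited form.

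- **Firm:** the outcome is undefined for randomised women who are never infused, and the early-access rule is a post-randomisation exclusion from an analysis called ITT.
- **Conditional on a literal reading:** the complete-case rule would drop women whose totals to discharge are known.
- **Wording only:** *received* in the primary comparison, and the description of what the CACE estimates.

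On size, the power effect is about 4 percentage points (83.6% − 79.5%). It arises only if the whole planned 10% is six-week loss among women with known totals. Bias cannot be sized from the article because no numbers are given for non-infusion, missed calls or early access. The 9% to 24% illustration rests on assumed normality and extreme one-sided loss. The reason to act is to avoid selective loss of randomised women. The protocol should be changed, but nothing here shows that the trial would be analysed as treated or would be underpowered.

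**What to change.** 1. Define the primary analysis set as every randomised woman with a known unit total to discharge, in her allocated arm, whatever her six-week status.
2. Define the start of the count for women never infused as randomisation. Alternatively, start at randomisation for all women and report the count from study medication alongside.
3. In Primary analysis, replace *received* with *were allocated to*.
4. Keep women whose results were accessed early in the primary analysis, and make their exclusion a sensitivity analysis. This concerns the analysis set only, not access to results.
5. Describe the CACE as the effect among compliers, using the outcome defined for all randomised women.

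**Cost.** Items 1, 3 and 5 and the narrow form of item 2 are clarifications of wording. Item 4 changes a stated rule for the analysis set. Moving the clock for all women is a change to the primary outcome and needs a documented amendment. It also adds slight noise from units given between randomisation and infusion, which should be balanced between arms in expectation while blinding holds. The present outcome already requires units to be placed before or after study medication, so the extra data burden should be small; the article does not state how transfusion times are recorded. By March 2014, 16 of 60 women had been randomised, and Baseline data says that analyses by arm wait until all follow-up is obtained, so the change can be made before any comparison.

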There are no systematic reviews of the use of fibrinogen concentrate in PPH; however, the fibrinogen level has been shown to be a useful predictor of progression from early to severe PPH in multiple studies. A fibrinogen level below 2.9 g/l, taken early during labour (before any bleeding has occurred), had an odds ratio of 19 for progression to PPH. In this study a fibrinogen of <2.9 g/l had a positive predictive value (PPV) of 39% for progression to PPH whilst a fibrinogen above 2.9 g/l had a negative predictive value (NPV) of 94% [13]. In other studies, a low fibrinogen level, taken early during a PPH, was predictive of the need for invasive procedures or infusion of RBC and FFP [14-16]. Charbit et al. found that a fibrinogen level below 2 g/l, taken during an on-going PPH, had a PPV of 100% for progression to severe PPH, defined in part as the need for at least 4 units of RBC, whilst a fibrinogen level above 4 g/l had a NPV of 85-90% [14]. Gayat et al. demonstrated that a fibrinogen level below 2 g/l, taken after a 1000 ml estimated blood loss, was an independent predictor for the need for an invasive procedure [15].

Retrospective data from 240 women experiencing a major PPH in a 6-month period, taken from the Cardiff Maternity Database, also found that fibrinogen was a useful predictor for progression to the need for RBC transfusion. The receiver-operator characteristic curve (ROC) area under the curve (AUC) (95% CI) for any RBC transfusion was 0.78 (0.74-0.83), the need for 4 units of RBC 0.8 (0.73-0.86) and for progression to 2500 ml blood loss 0.85 (0.78-0.93). In women with a fibrinogen level less than 3 g/l, 18/21 (86%) required RBC transfusion (median 3 units range 0–12) and 11 also required FFP. The mean (SD) allogeneic units (RBC + FFP + cryoprecipitate + platelets) infused was 5.8 (6.8). In contrast, in women with a fibrinogen level greater than 4 g/l (a normal level for delivery) 7/81 (8.6%) required RBC transfusion, a mean (SD) of 0.2 (0.6) units/woman, and none required FFP. These data have been confirmed in a prospective, consecutive cohort of 346 women in Cardiff experiencing a major PPH that showed that the ROC AUC (95% CI) for fibrinogen (*n* = 332) as a predictive biomarker for the need for 4 or more units of RBC transfusion was 0.77 (0.66-0.87).

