In the Cardiff prospective study there were 32 women with a Fibtem A5 below 16 mm (or a Clauss fibrinogen below 3 g/l) and on-going bleeding (>250 ml). Of these 27 (84%) required a red cell transfusion; mean (SD) number of units of red cells transfused was 4.1 (3.9). The mean (SD) number of units of allogeneic blood products was 8.2 (8.7). Of the 32 women, 7 also received between 3 and 7 g of fibrinogen concentrate as rescue haemostatic therapy.

Of the 288 women who had a Fibtem A5 of 16 mm or above or did not have on-going bleeding, and so would not have been randomised in the prospective study, 64 (22%) received a red cell transfusion, mean (SD) 0.55 (1.20 units/woman). The mean (SD) number of allogeneic units was 0.79 (2.19). The PPV (95% CI) for the need for a red cell transfusion of a Fibtem A5 below 16 mm in women with on-going bleeding was 84 (67–94)%. The NPV was 78 (73–82) %.

In the same study, of the 84 women with a Fibtem A5 of 23 mm or above, 16 (19%) received a red blood transfusion [median (range) 2 (2–5) units]. The mean (SD) number of units of red cells transfused was 0.44 (0.99) with a median (IQR) of 0 (0–0) units. The mean (SD) number of allogeneic units transfused was 0.58 (1.51) with a median (IQR) of 0 (0–0) units.

Although there is not a direct relationship between Fibtem and fibrinogen levels, in women experiencing major PPH, a Fibtem A5 of 16 mm is associated with a fibrinogen level below about 3 g/l and a Fibtem A5 of above about 23 mm with a fibrinogen above 4 g/l (prospective unpublished data from Cardiff and Huissoud 2009).

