### Secondary analysis

Secondary analysis includes investigating the effect of fibrinogen on:the total number of units of allogeneic products (red blood cells, FFP, cryoprecipitate and platelets) transfused within 24 h after study medication;the individual number of units of red blood cells, FFP, platelets and cryoprecipitate transfused after study medication within 24 h and until discharge;the total number of units of allogeneic products red blood cells, FFP, cryoprecipitate and platelets) plus 1 unit for every 250 ml cell salvage transfused within 24 h after study medication and until discharge,

and will be analysed using similar methods to those used in the primary analysis.

The effect of the intervention on the proportion of women receiving no allogeneic blood products, requiring cryoprecipitate or fibrinogen concentrate as subsequent therapy, and requiring invasive procedures, all within 24 h after the study medication and until discharge, will be examined by fitting logistic regression models again investigating for possible site-level clustering. The effect of fibrinogen on the incidence of exclusive breastfeeding will be explored using the same method.

Secondary outcomes also examined will be (1) the volume of cell-salvaged blood transfused within 24 h after the study medication and until discharge (2) and the measured abnormal blood loss within 24 h after study medication until discharge. These outcomes will be examined using linear regression models. Each of the regression model assumptions will be checked including but not limited to examining the distribution of the residuals and a plot of the residuals vs. predicted values. Similarly, Clauss fibrinogen and Fibtem parameters at 15 min and 24 h after the study medication will be examined between arms using a linear regression model adjusting for baseline measurements. The duration to (1) stopping breastfeeding or expressing breast milk and (2) any invasive procedure within 24 h after study medication and until discharge between arms will be examined using Cox’s proportional hazards model. Reasons for not exclusive breastfeeding will also be explored by using ordinal regression model.

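### The primary Poisson model makes no provision for overdispersion, although the article's own transfusion counts have variances about 4 to 9 times their means

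*Protocol article*

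**What the plan says.** The Primary analysis section compares total units of red cells, FFP, cryoprecipitate and platelets given after study medication until discharge. It states: "A Poisson regression model will be used with due emphasis placed on confidence intervals for the between-arm comparisons". The one addition that bears on the variance comes later in the same sentence: "with an investigation of site-level clustering". No scale parameter, robust variance or negative binomial model is mentioned. The Secondary analysis section says that the other unit counts "will be analysed using similar methods to those used in the primary analysis".

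The Background reports what such counts look like. It describes one subgroup of its prospective cohort thus: "there were 32 women with a Fibtem A5 below 16 mm (or a Clauss fibrinogen below 3 g/l) and on-going bleeding (>250 ml". The article then gives their transfusion total: "The mean (SD) number of units of allogeneic blood products was 8.2 (8.7" (8.7 being the SD). The retrospective cohort with fibrinogen below 3 g/l has 5.8 (6.8) units, and the prospective women with an A5 of 23 mm or above have 0.58 (1.51).

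The Sample size section recognises that the control-type counts are positively skewed: "The data were therefore transformed using the natural log (x + 1) transformation". It sizes the trial on a difference in means on that scale, not on a Poisson model.

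**The concern.** A Poisson model takes the variance to equal the mean and derives its standard errors from that. When the variance is several times the mean, the estimated ratio of means remains usable, but the default standard errors are too small by the square root of that multiple. The p-value and the confidence intervals, on which the plan places the emphasis, would then overstate the evidence, and chance differences between two arms of about 30 women could be reported as benefit or harm. The count secondary outcomes would inherit the fault.

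Overdispersion is to be expected here for a practical reason as well: products are given in batches (four units of FFP under Interventional phase, ten units of cryoprecipitate under Subsequent haemostatic therapy).

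**Working it through.** **1. The plan's own figure.** Inputs from Sample size: difference 0.775, SD 1.004 on the log(x+1) scale, two-sided 5%, power 80%.
n per arm = 2 × (1.96 + 0.842)² × 1.004² / 0.775² = 26.4, so 27; 54 / 0.9 = 60. The stated 27 and 60 reproduce, for a comparison of means on the log(x+1) scale.

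**2. Dispersion in the Background data.** φ = SD²/mean. If φ is the same in both arms, the true size of a nominal 5% Poisson Wald test is 2 × [1 − Φ(1.96/√φ)].

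| Women | Mean (SD) | Variance | φ | √φ | True size |
|---|---|---|---|---|---|
| Prospective, A5 <16 mm or Clauss <3 g/l, on-going bleeding (n = 32) | 8.2 (8.7) | 75.69 | 9.23 | 3.04 | 52% |
| Retrospective, fibrinogen <3 g/l (n = 21) | 5.8 (6.8) | 46.24 | 7.97 | 2.82 | 49% |
| Prospective, A5 ≥23 mm (n = 84) | 0.58 (1.51) | 2.28 | 3.93 | 1.98 | 32% |

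**3. Interval width at 8.2 (8.7), 27 per arm.** Poisson SE of the log ratio = √(2/(27 × 8.2)) = 0.095, so the 95% interval is the estimate ×/÷ exp(1.96 × 0.095) = 1.20. With the observed dispersion, SE = 0.095 × 3.04 = 0.289 and the factor is exp(1.96 × 0.289) = 1.76. On the log scale the Poisson interval has about one third of the correct width and covers about 48%, not 95%.

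**4. Simulated type I error under the null.** 27 per arm, 50,000 trials per scenario; 30 per arm gives almost the same.

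| Counts generated as | Poisson, default SE | Quasi-Poisson, t reference | Uncorrected sandwich, z reference | t-test on log(x+1) |
|---|---|---|---|---|
| Negative binomial, 8.2 (8.7) | 52% | 5.1% | 7.0% | 5.1% |
| Negative binomial, 5.8 (6.8) | 48% | 5.4% | 7.4% | 5.2% |
| Rounded counts from log(x+1) mean 1.811, SD 1.004 | 63% | 5.2% | 8.8% | 5.0% |

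The third scenario uses the Sample size section's own parameters. It implies a mean of about 9.1 and a variance of about 179, that is an SD of about 13.4, which is more than the 8.7 reported. It is best read as the heavy-tailed end of the range.

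**5. Candidate remedies.** A negative binomial likelihood-ratio test is close to nominal on negative binomial data (5 to 6%) but has 11 to 12% type I error in the third scenario. A sandwich variance with small-sample correction and t reference gives about 5.7 to 5.9% on negative binomial data at 8.2 (8.7), but about 7.5% in the third scenario.

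**6. Power.** With the third scenario's model, a log-scale difference of 0.775 and 27 per arm, quasi-Poisson has about 63% power. The log(x+1) t-test has close to 80% (79.5% by the noncentral t on the unrounded scale).

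**The case against.** The text says only that a Poisson regression model will be used. Quasi-Poisson and robust-variance versions are often given the same name, and an article may leave the variance estimator to an analysis plan that is not shown here. A reader might infer that the plan commits to unscaled standard errors and that the trial therefore has a 50% false-positive rate. The document does not support that: the figure is conditional on model-based standard errors. What remains is that the article names a model, emphasises its intervals and reports data that contradict the model's variance, and nothing in it corrects for this.

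The Secondary analysis section does say that model assumptions will be checked. That sentence follows the linear models, speaks of residual distributions and residual plots, and names neither dispersion nor a fallback. The investigation of site clustering concerns four centres and does not address variation between women.

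The cohort is a proxy. The Sample size section defines its control-type group by A5 alone and gives no raw mean or SD. The 8.2 (8.7) belongs to women with a low A5 or a low Clauss fibrinogen, 7 of whom also received fibrinogen concentrate, and the Background does not say when counting of units began. Treating the two groups as identical would be an inference. This limits the precision of the 50% but not the direction: the lowest dispersion in the table still gives about 32%.

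It is also tempting to conclude that negative binomial regression must become the primary model. Its size in the third scenario does not support that.

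**Conclusion.** The concern stands in conditional form. As written, the primary analysis makes no provision for overdispersion that the article itself documents. With default standard errors and trial counts dispersed like the cohorts, the nominal 5% test would reject a true null in roughly 30 to 60% of trials, about 50% at the 8.2 (8.7) values. This rests on three assumptions: model-based standard errors, similar dispersion in both arms under the null, and cohorts that are a fair guide to the trial. The first may already be settled otherwise in an analysis plan not shown. If so, the published wording still needs to say it. Because the primary p-value and intervals are affected and the repair is a matter of wording, it should be made before the analysis.

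**What to change.** Before unblinding, state one of two options for the primary analysis:

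- keep the Poisson model for the ratio of mean units, with a dispersion-scaled variance (quasi-Poisson) and a t reference distribution. This is the smaller change and held about 5% in all three scenarios above; or
- make the log(x+1) comparison that sized the trial primary, noting that it estimates a ratio of geometric means of x+1 and not a ratio of mean units.

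Prespecify the other option as the sensitivity analysis, or a negative binomial model or a small-sample-corrected robust variance, bearing in mind that the last two can exceed 5% if the counts are heavy-tailed. Apply the same rule to every count outcome under Secondary analysis.

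No new data or patients are needed. The costs are wider intervals and, if quasi-Poisson is primary, power of about 63% rather than the stated 80% at the planned effect under the log-scale model. The plan should state this loss openly.
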